## Abstract

**Background:** Coronary computed tomography angiography (CCTA) is a well-established key diagnostic modality for ruling out obstructive coronary artery disease (CAD) in patients with suspected chronic coronary syndromes (CCSs) and low to intermediate pre-test probability. The widespread availability of preprocedural CCTA data in CCS patients undergoing percutaneous coronary intervention (PCI), however, creates a new opportunity for image-guided procedural planning. **Objective:** The PRECISION-CT study (Prospective Evaluation of Coronary CTA Integration for Strategy Improvement and Optimization of Non-Emergent PCI) aims to evaluate the impact of CCTA-guided PCI on patient safety and clinical outcomes. **Methods:** PRECISION-CT is a prospective, two-center, randomized controlled trial, enrolling patients with CCS scheduled for elective PCI due to obstructive CAD by CCTA. Patients are randomized 1:1 to either CCTA-guided PCI or standard angiography-guided PCI. In patients randomized to CCTA-guided PCI, advanced post-processing of CCTA datasets provides specific procedural planning recommendations based on the detailed assessment of coronary artery takeoff, lesion location and plaque characteristics. In addition, real-time integration of the advanced CCTA post-processing is available in the catheterization laboratory during the PCI procedure. Patients randomized to angiography-guided PCI are treated according to routine clinical practice. **Results**: The primary endpoint is a composite procedural safety and efficacy score including: (i) need for intravascular imaging, (ii) procedural complications, (iii) post-procedural high-sensitivity troponin T elevation, (iv) contrast media, (v) radiation exposure, and (vi) length of hospital stay. Secondary endpoints include major cardiac adverse events such as cardiac death, non-fatal myocardial infarction, target-lesion reintervention and probable or definitive stent thrombosis during 1 year of follow-up. **Conclusions:** The PRECISION-CT study will provide pragmatic evidence on the ability of CT-guided PCI in patients with CCS to optimize procedural outcomes. These findings may help inform the broader adoption of image-guided precision revascularization strategies in interventional cardiology.

## 1. Introduction

Coronary computed tomography angiography (CCTA) has evolved to become a cornerstone of non-invasive cardiac imaging for patients with suspected chronic coronary syndromes (CCSs), based on current recommendations [1]. Its widespread adoption, particularly in the initial evaluation of patients, helps to rule out obstructive coronary artery disease (CAD) and to avoid unnecessary invasive coronary angiography (ICA) procedures in most patients with low to intermediate pre-test probability [2]. On the other hand, in patients with obstructive CAD, including those with high-grade (>90%) lesions or with intermediate lesions of functional significance, who are subsequently referred for ICA and percutaneous coronary intervention (PCI), CCTA datasets could be used to support pre- and periprocedural PCI planning [3].

This evolution presents a unique opportunity to enhance procedures by integrating anatomical and functional information derived from CCTA into the cardiac catheterization laboratory. Thus, beyond its diagnostic capabilities, CCTA offers a comprehensive assessment of coronary anatomy, including coronary artery takeoff, plaque morphology, lesion length, vessel size, and overall disease distribution [4,5,6,7]. These features are crucial in determining PCI complexity and for informing strategic decisions such as vascular access, stent selection and sizing, and the need for intravascular imaging or additional periprocedural lesion preparation techniques [4]. While randomized controlled trials such as the Precise Procedural and PCI Plan (P4) study are currently investigating the clinical equivalence of CT-guided PCI versus intravascular-imaging-guided PCI [4,8], real-world data on the practical implementation, feasibility, and impact of CCTA-guided PCI in routine practice remain limited [9]. To address this gap, the PRECISION-CT study (Prospective Evaluation of Coronary CTA Integration for Strategy Improvement and Optimization of Non-Emergent PCI) has been designed.

The aim of PRECISION-CT is to determine whether CCTA-guided PCI planning improves procedural strategy and execution in patients undergoing non-emergent revascularization. By integrating pre-PCI CCTA findings with procedural characteristics and clinical outcomes, the trial aims to clarify how CT-based planning can refine interventional strategies, reduce procedural uncertainty and reduce the need for intravascular imaging, thus optimizing resource utilization, procedural time, costs, patient safety, contrast volume, and radiation exposure. All these aspects may thereby ultimately introduce a more personalized and evidence-based approach to PCI. Figure 1 summarizes the methodological aspects and flowchart of the trial. 

Importantly, the PRECISION-CT study evaluates the incremental value of structured, quantitative, and real-time CCTA integration into the catheterization laboratory compared with standard-of-care CCTA-informed PCI. This design reflects contemporary clinical practice, where CCTA is frequently available prior to ICA, and focuses on whether enhanced integration of existing imaging data can improve procedural planning, efficiency, and safety.

## 2. Materials and Methods

### 2.1. Study Design and Setting

The PRECISION-CT study is an investigator-initiated, prospective, randomized, dual-center clinical trial designed to evaluate the impact of extended CCTA analysis on procedural planning and outcomes of PCI. The trial will be conducted at the GRN Hospital Weinheim, Germany, with image post-processing and advanced CCTA analyses performed at the University Hospital Zurich (USZ). Data transfer and analysis will be carried out according to Good Clinical Practice (GCP) standards and the Declaration of Helsinki. The study protocol has received approval from the local ethics committee (S-436/2025) and is registered in the German Registry of Clinical Studies (DRKS00038939). All participants will provide written informed consent prior to enrollment. Patient safety will be ensured via bail-out criteria, documentation of omitted measures, and monitoring of complications by the hospital’s steering ethics committee.

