### 2.7. PCI Procedure and CT-Guided Planning

Interventional cardiologists will receive a standardized CCTA report prior to the PCI procedure during the pilot study phase for all patients and during the randomized study for the patients randomized to the CCTA-guided PCI arm. The report contains annotated images and textual descriptions covering optimal angiographic projections, reference vessel diameters, lesion length, calcium distribution, and bifurcation anatomy to guide stent and device selection. A representative file report is provided in the Supplementary Materials, illustrating how quantitative and actionable information is communicated consistently to the operator. Procedural planning includes:•Maximal Intensity Projection (MIP) images of the coronary tree.•Exact location and height of coronary ostia.•Axial images of coronary arteries.•Multiplanar reformation (MPR) images of coronary arteries.•Short-axis cross-sectional images.•Lesion length.•Bifurcation anatomy and vessel tortuosity, as well as a suggested provisional stenting versus a two-stent approach.•Calcification burden, including the arc of the calcification in degrees and the calcification length.•Lesion morphology, including the presence and extent of mixed and non-calcified plaques.•Optimal C-arm angulation angles.•The need for lesion preparation (rotational atherectomy or intravascular lithotripsy), choice of guiding catheter, stenting strategy, and projection angles may be adapted accordingly.

Intravascular imaging will not be discouraged in either study arm and will be encouraged in both arms in certain clinical scenarios and based on current guideline recommendations. Thus, operators may perform IVI based on pre-specified bail-out criteria, including uncertain lesion length or morphology, suboptimal stent expansion or malapposition, complex bifurcation anatomy, heavy calcification, or any safety concern. All IVI use, including specific indications for imaging, will be prospectively documented. Notably, the “need for IVI” in the composite endpoint reflects procedural escalation and resource utilization and not an adverse clinical event.

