### 2.8. Data Collection

Data will be collected prospectively and will be entered into a standardized database. The collected variables include:▪**Demographics**: age, gender, date of admission, and length of hospitalization.▪**Indications for CCTA and ICA**: typical angina pectoris, atypical angina pectoris, non-anginal chest pain, or presence of dyspnea.▪**Medical history and cardiovascular risk factors**: prior myocardial infarction, hypertension, dyslipidemia, diabetes mellitus, current or prior cigarette smoking, chronic obstructive pulmonary disease, chronic kidney disease, atrial fibrillation, or peripheral artery disease.▪**Cardiac medications at baseline.**▪**Echocardiographic data**: left ventricular ejection fraction (LVEF) or presence of regional wall motion abnormalities.▪**CCTA data:**oAnatomic lesion location, including segment number and classification into proximal, mid, or distal vessel.oOstial involvement and measurement of coronary ostium height from the aortic annulus.oTakeoff angle of right and left coronary ostia, assessed using clock-face reference.oPlaque composition (calcified, non-calcified or mixed based on the presence of the calcified content by visual criteria of >80%, 20–80% and <20% calcium content) [12].oPresence of high-risk plaque features, including: positive remodeling, napkin-ring sign, low attenuation plaque (<30 HU) or spotty calcification [13].oTotal coronary calcium score quantified using the Agatston score.▪**Invasive procedural data**: Comprehensive data from invasive coronary procedures will be collected, including: use of advanced intracoronary imaging (IVUS if necessary), use of physiological assessment (FFR or iFR/RFR if necessary), number of stents implanted, their total length, stent diameters, the use of re-dilation, including the use of scoring balloons and the corresponding pressures, and the use of lesion modification techniques (rotablation or/and intravascular lithotripsy), and bifurcation stenting strategies including provisional versus bifurcation stenting if necessary.▪**Procedural outcomes and metrics**: Final TIMI flow grade, residual stenosis in percentage, procedural success, defined as final TIMI 3 flow with <20% residual stenosis in the treated segment and absence of in-hospital major adverse procedural events, additional procedural metrics included total fluoroscopy time (minutes), radiation exposure (mGy), contrast volume used (ml), and total procedure duration (minutes).▪**Operator feedback and satisfaction:**oUse of CT-based projections during PCI.oPrediction of stent dimensions (length and diameter) based on CCTA measurements.oPrediction of landing zones for stent deployment.oSatisfaction with CCTA planning (1–5 scale for both primary and secondary operators).oPerceived benefit of CCTA-derived data on ostial angle, lesion length, plaque quality and projection guidance, helping with reducing procedure time, fluoroscopy exposure and complications.oWhether CCTA planning helped in avoiding unnecessary PCI or reducing the number of stents required for lesion treatment.

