
### 2.9. Study Endpoints

Primary composite endpoint (score 0–6):

The primary composite endpoint was designed to capture procedural efficiency and safety rather than long-term clinical outcomes. Individual components were selected to reflect aspects of PCI that may be directly influenced by improved preprocedural anatomical understanding and planning, including resource utilization, procedural complexity, and periprocedural myocardial injury. The composite score is intended as a pragmatic measure of procedural optimization rather than a surrogate for clinical outcome.

Need for intravascular imaging (IVUS).Occurrence of major procedural complications (perforation, severe dissection, stent malapposition, or under-expansion requiring post-dilatation, main/side branch occlusion).Post-procedural high-sensitivity troponin T elevation >5-fold compared to baseline at 24 h.Contrast volume > 200 mL as established in prior interventional studies.Radiation dose > predefined threshold (estimated effective dose of >16.1 mSv) according to institutional and published reference levels for PCI procedures [14].

Hospital stay > 2 days. Secondary endpoints (exploratory):

In-hospital MACE and complications or the need for repeated cardiac catheterization with or without reintervention during the index hospitalization or within 30 days after the procedure.

Long-term major adverse cardiac events (MACE): cardiac death, probable or definitive stent thrombosis, non-fatal myocardial infarction, or target-lesion revascularization at 12 and 24 months.

Guiding catheter changes or unplanned use of lesion preparation techniques.

Procedural efficiency metrics (procedure duration, fluoroscopy time, material consumption, and cost-effectiveness).

Patient-reported outcomes: quality of life using the SAQ-7 questionnaire.

Clinical events and complications are defined according to established consensus criteria, including Academic Research Consortium (ARC) definitions for stent thrombosis and target-lesion failure and Society for Cardiovascular Angiography and Interventions (SCAI) criteria for procedural complications. Imaging-derived findings are reported separately and are not classified as clinical events unless they meet these standardized definitions.

Figure 1 summarizes the methodological aspects and flowchart of the trial.

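### Item 1 of the primary score is named need for intravascular imaging but counts imaging performed, so imaging left out with a bail-out criterion present scores as benefit

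*Protocol article*

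**What the plan says.** Five parts of the protocol article bear on this.

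- **Safety (section 2.1).** "Patient safety will be ensured via bail-out criteria, documentation of omitted measures, and monitoring of complications by the hospital’s steering ethics committee". What counts as an omitted measure is not said, and neither an arm nor a procedure is named.
- **When IVI is done (section 2.7).** "Intravascular imaging will not be discouraged in either study arm and will be encouraged in both arms in certain clinical scenarios". The text continues: "operators may perform IVI based on pre-specified bail-out criteria, including uncertain lesion length or morphology, suboptimal stent expansion or malapposition". The list goes on to complex bifurcation anatomy, heavy calcification and any safety concern. The verb is permissive.
- **What is recorded (sections 2.7 and 2.8).** "All IVI use, including specific indications for imaging, will be prospectively documented". The procedural data list has "use of advanced intracoronary imaging (IVUS if necessary").
- **What is scored (sections 2.9 and 2.7).** The first of six components is "Need for intravascular imaging (IVUS"). Section 2.7 explains that this item "in the composite endpoint reflects procedural escalation and resource utilization and not an adverse clinical event".
- **Who decides (section 2.6).** Operators cannot be blinded and learn the allocation just before the procedure. The Introduction lists less need for IVI among the aims of the trial.

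**The concern.** The name of item 1 and the quantity scored are different things. Need is a state of the patient and the lesion. Use is a decision by the operator. They agree only if IVI is done whenever it is needed and not otherwise. Here an unblinded operator decides, under criteria that permit imaging without requiring it, in a trial that aims to show less of it.

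A lower score on item 1 in the CCTA arm then has two possible sources. One is the hypothesis: better planning leaves fewer uncertain situations. The other is that the same situations arose and imaging was not done. The score treats both as the same gain. The record of omitted measures is the natural means of telling them apart, but the article links it to neither the bail-out criteria nor the IVI data items. If criterion status is not captured prospectively in patients without IVI, a later table or analysis plan cannot fully recover it.

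**Working it through.** **Step 1: what item 1 can distinguish.** The article spells out no scoring rule. Scored from IVI performed, as section 2.7's explanation implies, item 1 gives:

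| Bail-out criterion | IVI done | Item 1 |
|---|---|---|
| absent | no | 0 |
| present | yes | 1 |
| present | no | 0 |

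The first and third rows cannot be told apart from the score. A record of IVI use and its indication does not separate them either, because an indication is tied to imaging that took place.

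**Step 2: the plan's own figure.** Section 2.11 assumes an event rate of about 50%, a 20-point absolute reduction, 100 per arm and two-sided α of 0.05, and claims power above 80%. With p1 = 0.50, p2 = 0.30 and mean 0.40:

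z = (0.20 × √100 − 1.96 × √(2 × 0.40 × 0.60)) / √(0.25 + 0.21) = (2 − 1.358) / 0.678 = 0.947, so power is 82.8%.

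Exact enumeration of the chi-square test gives 83.2%. The stated power reproduces, and this point does not depend on it. The figure only provides a scale for what follows.

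**Step 3: possible size in item 1.** The document gives no rate for bail-out criteria or for IVI use, so every input here is assumed.

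Spurious gain = share with a criterion present × (IVI use given criterion, control minus CCTA arm).

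- Central case: 40% with a criterion in each arm, IVI then done in 80% (control) and 50% (CCTA). Item 1 is 0.40 × 0.80 = 32% versus 0.40 × 0.50 = 20%, a gain of 12 points with equal need. Criterion present without IVI: 40 × 0.20 = 8 versus 40 × 0.50 = 20 patients per 100.
- Range: 0.30 × 0.15 = 4.5 points to 0.50 × 0.30 = 15 points.

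**Step 4: carried to the composite.** Assume further that an event is at least one point, and that 30% to 40% of patients score on another item, independently of item 1.

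Effect on the composite = gain in item 1 × (1 − share scoring elsewhere).

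- Range: 0.045 × 0.60 = 2.7 points to 0.15 × 0.70 = 10.5 points, against the planned 20.
- Central case with 30% scoring elsewhere: control 1 − 0.70 × 0.68 = 52.4%, CCTA 1 − 0.70 × 0.80 = 44.0%, a difference of 8.4 points. The control rate is close to the plan's 50%.

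**Step 5: effect on the test.** Take no true effect (50% in both arms, 100 per arm). Let x be the share of CCTA-arm patients who would score only on IVI, had a criterion present and were not imaged. Exact chi-square rejection rates:

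| x | Trials declaring a difference |
|---|---|
| 0 | 5.6% |
| 5% | 11.8% |
| 10% | 31.0% |
| 15% | 58.7% |
| 20% | 83.2% |

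The assumed range in step 4 reaches up to about x = 10%.

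**The case against.** The case on the other side is substantial, and parts of it stand.

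- **Omissions are to be documented.** A reader might infer that skipped imaging goes unrecorded. The document does not support that: section 2.1 commits to documenting omitted measures, which can include IVI, and section 2.8 says only what the variables include. What remains is that the record is undefined and unconnected to the criteria.
- **No analysis of that record is described.** In a condensed article this is no finding by itself. Tabulating a safety log is commonly left to the full protocol or analysis plan, which are not shown.
- **Some criteria are captured anyway.** Section 2.11 plans subgroup analyses by calcification severity, bifurcation involvement and lesion complexity, so these features must be known in both arms. This stands for the anatomical criteria. It does not cover uncertain lesion length or morphology, or a safety concern.
- **The article explains the item.** For resource use, use is the right quantity. That is fair, and it is a reason to name the item accordingly. It does not let a lower rate be read as less need.
- **Not imaging is not defined as harm.** Correct. The criteria permit IVI, so its absence is neither a deviation nor shown to be harmful. The point concerns what the score can show.
- **Other endpoints catch consequences.** In part. Troponin, repeat catheterization and MACE are collected, and item 2 counts "Occurrence of major procedural complications (perforation, severe dissection, stent malapposition, or under-expansion requiring post-dilatation, main/side branch occlusion"). MACE is exploratory, however, and malapposition or under-expansion is probably harder to detect without IVI. That last point is a judgement; the document does not state it.

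Section 3 acknowledges performance bias from unblinded operators, but in general terms and not for this item.

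**Conclusion.** The point holds in a limited form. Item 1 is labelled need and scored as use, the decision is unblinded and discretionary, and imaging left out with a criterion present improves the score of the arm where it happens. The record that could show this is promised but not defined.

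The size is unknown. The 4.5 to 15 points on item 1, the 2.7 to 10.5 points on the composite and the rejection rates all rest on assumed need, assumed differential use, independence of the items and an event defined as at least one point. They show that the mechanism could matter against a planned 20-point effect. They are not an estimate of expected bias, and nothing in the document indicates that operators will omit more imaging in the CCTA arm. A reader might also infer that the trial cannot detect harm from omitted imaging at all. The collected complications, troponin and follow-up events do not support so strong a statement.

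This should be corrected before randomized patients are enrolled, because the missing information has to be captured at the procedure.

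**What to change.** - **Sections 2.7 and 2.8:** define the omitted-measures record so that, for every patient in both arms, the presence of each bail-out criterion already listed (yes/no) and whether IVI was done are captured prospectively. Take the anatomical criteria from CCTA or angiographic data where possible.
- **Section 2.11:** report criterion present with IVI not done by arm, as counts with a risk difference and 95% CI, together with IVI use among patients with a criterion present.
- **Section 2.11:** add a sensitivity analysis of the primary score without item 1, and read a lower IVI rate as reduced need only alongside that table.
- **Section 2.9:** describe item 1 as IVI use.

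Rescoring item 1 as positive whenever a criterion is present is not advised as the main remedy. Calcification and bifurcation are baseline anatomy that the intervention cannot change, so they would pull the item toward no difference by construction.

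The cost is a few form fields, also completed when no IVI is done, one table and one sensitivity analysis. It needs no extra patients or procedures. One weakness remains: the subjective criteria are still judged by the unblinded operator. No change to when IVI is performed is proposed.

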### 2.2. Patient Population

Eligible patients are adults (≥18 years) with suspected CCS who undergo clinically indicated CCTA and are subsequently referred for ICA based on CCTA findings. Recruitment will be performed consecutively among patients undergoing clinically indicated CCTA at the GRN Hospital Weinheim (approximately 700 annually). Patients will be informed about this study during the standard ICA consent process.

